### Outcome measures

A logic model provides the framework for the evaluation (see Figure 1). This proposes causal pathways that link together the implementation of the POS legislation with a set of short-term, intermediate and long-term outcomes which will be assessed by the various study components. Therefore, rather than defining primary and secondary outcomes, we have set out a timeframe within which we believe the outcomes will occur. We have classified outcomes as *short-term*, if they were likely to occur within 3 months of implementation of the legislation*; intermediate*, if they were likely to occur up to one year post-implementation; and *longer-term* if they were likely to occur more than a year post-implementation.

**Figure 1 F1:**
[figure not shown]
Logic Model of Activities, Outputs and Outcomes Associated with Point of Sale (POS) Legislation.

Short-term outcomes of interest are prevalence of POS advertising in tobacco retail outlets (assessed by components 1 and 2) and exposure to POS advertising (assessed by components 1, 2 and 3).

Intermediate outcomes of most interest are awareness of point of sale advertising, cigarette brand awareness, perceived ease of access to cigarettes, attempts to purchase cigarettes, perceived youth smoking prevalence, and pro-tobacco attitudes. Long-term outcomes of most interest are: incidence and prevalence of smoking.

Data obtained through interviews with members of the retailer panel (component 2) and focus group discussions with pupils will provide qualitative data for all the intermediate outcomes.

In addition to the outcomes outlined above, the study design will also enable us to identify any unintended or adverse consequences associated with the legislation, such as an increase in purchases from black market sources or proxy purchases; and the introduction of new strategies by retailers or the tobacco industry to circumvent the regulations. In Ireland, for example, images of tobacco-related paraphernalia such as cigarette lighters regularly appear on the blank covers of the cigarette gantries.

### Sample size and power calculations for school surveys

Table 2 below gives our estimated sample sizes and smoking prevalence and incidence for each of the school survey waves. The numbers of current and ever smokers are extrapolated from data from the 2008 Scottish Schools Adolescent Lifestyle and Substance Use Survey (SALSUS) National Report [18], the Health Behaviours of School Children (HBSC) 2010 Scotland National Report [19], and the 2008 Scottish Health Survey Data [20].

**Table 2 T2:** Estimated sample sizes and smoking prevalence and incidence by age and year group

**Age group/Grade**	**% pupils in each class**^ **1** ^	**N pupils per school**	**Tot no pupils 4 schools**	**Estimated response rates**^ **2** ^		**Prevalence regular smoking**^ **3** ^		**Incidence regular smoking**	**Prevalence ever smoked**		**Incidence ever smoked**
				**%**	**N**	**%**	**N**		**%**	**N**	
School Surveys 2013-14											
13/S2	100%	188	752	85%	640						
15/S4	100%	188	752	85%	640						
Total all schools		376	1504	85%	1280						
Total per school			376	85%	320						
School Surveys 2015-17											
12/S1	18.1%	217	866	85%	736	1.0%	7	1.0%	4%	26	4%
13/S2	18.3%	220	878	85%	747	4.8%	35	3.8%	23%	168	19%
14/S3	18.8%	225	902	85%	767	11.0%	84	6.3%	35%	268	13%
15/S4	18.8%	225	901	85%	766	16.5%	126	5.5%	44%	333	9%
16/S5	15.7%	189	754	85%	641	20.0%	128	3.5%	47%	298	3%
17/S6	10.2%	123	491	85%	417	24.0%	100	4.0%	47%	194	0%
Total all schools		1198	4793		4074		482			1287	
Per School			1198		1018		120			322	

1. Distribution of pupils over different age groups is based on most recent School statistics released by Scottish Government.

2. Response rates are based on HBSC survey experience.

3. Regular smoking defined as weekly smoking. Percentage 13 and 15-year old based on SALSUS, Percentages 12, 14, 16 and 17-year olds based on plotting, making use of HBSC smoking data for 11-year olds, SALSUS 13 and 15-year olds and 17-year olds’ data from the Scottish health survey (16-24-year olds: Male 24%; Female 29%) [18-20].

Table 3 provides detailed power calculations for cross sectional analyses of the main intermediate and long term outcomes for i) the surveys of S2 and S4 school children that will be conducted in 2013 and 2014 and, ii) the whole school surveys that will be conducted between 2015 and 2017. The estimates are based on an average school roll of 1200 pupils and 85% attendance on the day of the survey.

**Table 3 T3:** Power calculations for intermediate and long-term outcomes

			**Sample size required at 0.80 power with two-tailed test**		**Sample before and 1 year after POS Supermarket (4 S2 & 4 S4 from 4 schools 24 pupils each class 85% response rate)**		**Sample before Small Shops POS and 2 years after (all pupils attending schools, 4 schools, school size 1200 pupils, response rate 85%)**	
	**Outcome**	**Change**	**p < .05**	**p < .01**	**4 schools combined**	**Urbanisation (2 levels)**	**4 schools combined**	**Urbanisation (2 levels)**
						**Deprivation (2 levels)**		**Deprivation (2 levels)**

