## Methods/design

The study has a multi-modal before and after design and uses mixed methods to collect data in four purposively selected communities. For the purposes of the study, community is defined as the catchment areas of the secondary schools selected for study. Schools were purposively selected to reflect two levels of urbanisation (large urban vs. small town) and two levels of socio-economic deprivation (high vs. medium or low). Deprivation categories were derived from the population-weighted mean Scottish Index of Multiple Deprivation (SIMD) score for all data zones falling within the school catchment areas and the proportion of children from each school receiving free school meals. To keep the influence of school factors, other than urbanisation and deprivation, to a minimum, the selected schools were non-denominational local authority schools on mainland Scotland with an ethnic minority population of less than 10% of the school roll. In addition, schools were also selected to have a pupil roll of between 1100 and 1200.

There are four main components to the study. In each community we are conducting:

•Mapping and spatial analysis of the location and density of tobacco retail outlets.

•Tobacco advertising and marketing audits of tobacco retail outlets most used by young people, supplemented by interviews and observations with a panel of retailers in four matched communities.

•Cross-sectional school surveys of pupils, with five embedded pupil cohorts.

•Focus group interviews with purposive samples of pupils.

Data for the study components were collected at baseline between February and April 2013, prior to implementation of the legislation on 29^th^ April 2013. Follow-up data collection will be repeated annually for four years. Additional marketing audits were conducted immediately post-legislation in May 2013 to assess compliance in large retail outlets and this will be repeated in May 2015 in smaller retail outlets, following implementation of the POS legislation in smaller retailers in April 2015.

Details of the study components are as follows:

1. Annual mapping and spatial analysis studies of tobacco retail outlets

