3 Starting percentages based on findings latest published results from HBSC [19] and SALSUS [18] studies.

4 Starting percentages based on findings latest published results from SALSUS [18].

* Denotes power calculation for a one-tailed test. Blank cells are underpowered to detect a significant change.

The estimated baselines and changes in access to tobacco; awareness of tobacco marketing; perceived prevalence of youth smoking; and ease of access to tobacco are based on the evaluation of POS ban in Ireland. [14] The baseline percentages for other intermediate outcomes outlined in below are derived from data from the 2008 Scottish Schools Adolescent Lifestyle and Substance Use Survey (SALSUS) National Report [18] and the Health Behaviours of School Children (HBSC) 2010 Scotland National Report [19]. Power calculations are given for all pupils (community populations), current smokers and ever smokers. An asterisk denotes power calculation for a one-tailed test. Blank cells are underpowered to detect a significant change.

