### Data analysis

An advantage of adopting a spatial approach to data collection is that the various quantitative datasets can be readily integrated into a GIS. By collecting postcodes, the retail outlets, audits (retailer panel and discreet) and the school survey information will each be geographically referenced. This will enable us to integrate the data into a single database for further quantitative analysis.

The primary analyses around implementation in large retailers will focus on estimating the reduction in POS advertising between February and April 2013 (baseline) and February-to April 2014 and the relationship between POS exposure and awareness of POS advertising and changes in perceived access to tobacco and perceived youth smoking prevalence. In addition to the above, the primary analyses around implementation in smaller retailers will also examine the impact of full implementation on behavioural outcomes including purchase of tobacco products and smoking incidence and smoking prevalence. Specifically, we will:

•Examine changes in exposure to tobacco advertising, access to tobacco products and attitudes towards smoking between baseline (February to April 2015) and the same months in 2016 and 2017 for the total sample, with sub-group analyses by community deprivation, urbanisation and baseline availability of cigarettes.

•Examine changes in incidence of regular smoking and smoking prevalence between baseline (February to April 2015) and the same months in 2016 and 2017, with sub-group analyses by community deprivation, urbanisation and baseline availability of cigarettes.

•Assess if there is a of a dose-response relationship between changes in POS advertising or changes in availability of cigarettes and other study outcomes. To do this, we will create continuous dummy variables for various measures of advertising exposure which can be used in the analyses.

Given the number of outcomes we wish to examine, in the analyses we will set a higher statistical significance threshold (type I or α error) where possible.

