## Discussion

The POS legislation presents a unique opportunity to examine the impact of a public health policy and, as far as we are aware, this is the first study to robustly assess the impact of a partial and comprehensive ban of POS tobacco advertising on youth attitudes to smoking, perceived access to tobacco products and smoking prevalence. In addition, we will also monitor compliance with the legislation and changes in tobacco retailing and marketing activity, as well as any unintended consequences associated with the legislation, such as new tobacco industry tactics and black-market sales. We have developed a systematic and robust evaluation that overcomes many of the methodological problems inherent in a natural experiment. Through careful design of a multi-component study we will be able to assess differential impacts associated with the legislation by both community deprivation and individual measures of socio-economic status. We will also develop novel approaches, both to the measurement of exposure to point of sale tobacco advertising and depicting changes in spatial and temporal distribution of some of the potential determinants of health inequalities.

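### Table 3 treats pupils from four schools as independent, so it overstates power for smoking prevalence, smoking incidence and the small-effect two-school subgroups

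*Protocol article*

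**What the plan says.** The study "uses mixed methods to collect data in four purposively selected communities", and "community is defined as the catchment areas of the secondary schools selected for study". The Methods/design section selects the schools on two levels of urbanisation and two of deprivation, so each level holds two schools.

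The sample-size section says that "Table 3 provides detailed power calculations for cross sectional analyses of the main intermediate and long term outcomes". The table has columns headed "Sample size required at 0.80 power with two-tailed test", at two significance levels. It then gives the power from 1280 pupils per wave (2013-14) and 4074 per wave (2015-17), and from half of each for the subgroups. Its footnote reads "Denotes power calculation for a one-tailed test. Blank cells are underpowered to detect a significant change". No ICC, design effect or effective sample size appears. The only multi-level approach mentioned concerns the synthesis of quantitative and qualitative findings.

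The Data analysis section plans analyses of change "with sub-group analyses by community deprivation, urbanisation and baseline availability of cigarettes". The Discussion says "we will be able to assess differential impacts associated with the legislation by both community deprivation and individual measures of socio-economic status".

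**The concern.** Pupils in one school share retailers, peers, staff and local events. Because the same schools are surveyed before and after, a school that always smokes more than the others does no harm to the estimate of change. A school whose smoking rate drifts between waves for its own reasons does. That drift does not average out over a thousand pupils in the school, only over schools, and there are four (two per level of urbanisation or deprivation). A power calculation that counts pupils alone leaves it out.

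The table matters because the Background criticises the Irish evaluation as too small to detect a change in prevalence, and Table 3 is this study's evidence that it can do better. If its entries are too high, a null result on smoking will seem more informative than it is.

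A second issue needs no ICC. Power to detect a change within the deprived schools is not power to show that the change differs from that in the other schools.

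**Working it through.** **1. Reproducing the table.** With d = p1 − p2 and p̄ their mean, the number per wave is

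n₀ = [1.96·√(2p̄(1−p̄)) + 0.84·√(p1(1−p1) + p2(1−p2))]² / d²,

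and with continuity correction n = (n₀/4)·[1 + √(1 + 4/(n₀d))]². At the 1% level, 2.576 replaces 1.96.

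| Outcome | n₀ (5%) | n (5%) | Table 3 (5%) | n (1%) | Table 3 (1%) |
|---|---|---|---|---|---|
| Access 32%-25% | 651.6 | 679.9 | 680 | 998.3 | 999 |
| Incidence, regular 4%-2% | 1140.8 | 1238.8 | 1239 | 1796.5 | 1797 |
| Incidence, any 9%-7% | 2887.2 | 2986.4 | 2987 | 4395.9 | 4396 |
| Prevalence 13%-10% | 1774.0 | 1840.0 | 1841 | 2706.2 | 2707 |
| Prevalence 13%-9% | 959.3 | 1008.7 | 1009 | 1477.4 | 1478 |

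Rounded up, all ten all-pupil rows agree at both levels. The design effect used is therefore 1.

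The stated powers also follow from the raw pupil counts, using Φ[(d − 1.96·SE₀)/SE₁] without continuity correction, where SE₀ uses the pooled proportion and SE₁ the separate ones. For 13%-10% at N=2037, SE₀ = SE₁ = 0.0100, so (0.030 − 0.0196)/0.0100 = 1.04 and power is 0.85 (stated >0.80). At N=4074 it is 0.989 (stated >0.99). For 4%-2% at N=1280 it is 0.84 (stated >0.80).

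**2. Allowing for school-by-wave variation.** Effective N = N / [1 + (m − 1)ρ], where m is pupils per school per wave: 4074/4 ≈ 1018, or 1280/4 = 320. Here ρ covers only the part of the school effect that changes between waves: the ICC times one minus the between-wave correlation of school effects. For example, an ICC of 0.02 with a correlation of 0.9 gives ρ = 0.02 × 0.1 = 0.002. The protocol gives none of these values, so ρ is an assumption shown as a range.

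Design effects at ρ = 0.0005 / 0.001 / 0.002 / 0.005 are 1.51 / 2.02 / 3.03 / 6.09 for m = 1018, and 1.16 / 1.32 / 1.64 / 2.60 for m = 320. For scale, at prevalence 11.5% and ρ = 0.001 the drift has a standard deviation of √(0.001 × 0.115 × 0.885) = 0.010, or one percentage point per school and wave.

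| Table 3 cell | Stated | ρ=0.0005 | 0.001 | 0.002 | 0.005 |
|---|---|---|---|---|---|
| Prevalence 13%-10%, N=4074 | >0.99 | 0.93 | 0.85 | 0.68 | 0.41 |
| Prevalence 13%-10%, N=2037 | >0.80 | 0.69 | 0.56 | 0.41 | 0.23 |
| Prevalence 13%-9%, N=1280 | >0.80 | 0.85 | 0.81 | 0.72 | 0.52 |
| Incidence 4%-2%, N=1280 | >0.80 | 0.79 | 0.73 | 0.64 | 0.45 |
| Incidence 4%-2%, N=2037 | >0.80 | 0.86 | 0.75 | 0.58 | 0.33 |
| Access 32%-25%, N=640 (two schools) | 0.80 | 0.73 | 0.68 | 0.58 | 0.41 |

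The largest ρ that keeps 0.80 is 0.0013 for 13%-10% at N=4074, 0.00015 for the same change at N=2037, and 0.0004 for 4%-2% at N=1280.

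**3. Cells that survive.** Awareness 81%-22% stays above 0.99 throughout. At ρ = 0.002 and N=4074, access 32%-25% keeps 0.98 and perceived prevalence 62%-52% stays above 0.99. The 13%-9% subgroup cell (N=2037) is 0.98 under independence and 0.82 at ρ = 0.001.

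**4. Difference in change.** Suppose prevalence falls from 13% to 10% at one deprivation level and stays at 13% at the other, with 2037 independent pupils per level and wave. Then SE = √[(3 × 0.1131 + 0.0900)/2037] = 0.0145, z = 0.030/0.0145 = 2.07 and power is Φ(2.07 − 1.96) = 0.54. Table 3 shows >0.80 for the within-level change.

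**The case against.** The strongest reply is that the loss rests on an assumed ρ, and that the schools were chosen purposively. If inference is confined to these four schools and they have no time shocks of their own, the printed powers stand. That is correct, but the protocol states no such restriction and sets out to assess the impact of national legislation.

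Several stronger readings that a reader might infer are not supported:

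- *All of Table 3 is unreliable.* It is not: large-effect intermediate outcomes keep high power at ρ = 0.001 to 0.002. The 2013-14 Age subgroup also has all four schools at each level.
- *Repeated pupils make the overstatement worse.* They work the other way, because positive within-pupil correlation, when modelled, makes a change more precise. By Table 2, years S3-S6 are (767 + 766 + 641 + 417)/4074 = 64% of a 2017 wave and could have been surveyed in 2015. With an assumed correlation of 0.3 to 0.5, 13%-10% at N=4074 and ρ = 0.001 rises from 0.85 to about 0.88 to 0.90. In 2013-14 only S2 and S4 are surveyed, a year apart, so the same cohorts do not recur.
- *Power should come from a t test on four or two school-level changes.* The Data analysis section plans no such test, so its low power is not an error in Table 3.
- *The analysis itself will ignore clustering.* The article shows independence in the power calculation only; the model may be set out in a document not shown.
- *The third research question requires a difference in change.* It asks about socio-economic patterning, which need not mean that. The Discussion's claim of differential impacts does.

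The Discussion also concedes the uncontrolled design and plans internal-control outcomes, dose-response analysis and triangulation. These help interpretation but do not correct a power figure.

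**Conclusion.** The point holds in a limited form. Table 3 assumes a design effect of 1, which is established by exact reproduction. Any positive school-by-wave variance makes its powers too high. The loss is material for smoking prevalence, smoking incidence and the small-effect urbanisation and deprivation cells. At an assumed ρ of 0.001, 13%-10% falls from 0.99 to 0.85 with all pupils and from 0.85 to 0.56 in a two-school subgroup, and 4%-2% at N=1280 falls from 0.84 to 0.73. The direction is certain for any positive ρ; the size depends on a value that the protocol does not supply.

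The mismatch between within-level power and the claim of differential impact stands without any assumption about ρ. In the example, the contrast that the claim needs has power 0.54, and two schools against two cannot separate deprivation from whatever else distinguishes those schools.

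**What to change.** - State beside Table 3 that it assumes independent pupils. Restate the affected powers (smoking prevalence, smoking incidence, small-effect urbanisation and deprivation cells) over a range of school-by-wave ρ, for example 0.0005, 0.001, 0.002 and 0.005.
- Let the analysis of change allow for school-by-wave variation.
- Test differential impact by a wave-by-subgroup interaction instead of reading it from separate within-level results. Make wave by pupil-level socio-economic status, within schools, the main test; the Discussion already names individual measures. Label the two-versus-two-school deprivation contrast as descriptive.

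The cost is a less favourable power table and minor analysis work. No new data, schools or survey waves are needed.

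### Table 3: seven required-n entries do not belong to the change printed beside them, and two ever-smoker cells marked above 0.80 fall short of it

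*Protocol article*

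**What the plan says.** In the section on sample size and power for the school surveys, the protocol article states: "Table 3 provides detailed power calculations for cross sectional analyses of the main intermediate and long term outcomes". Table 3 gives each outcome a before-after change, then two columns of required n (p<.05 and p<.01) headed "Sample size required at 0.80 power with two-tailed test", then power at the expected N. The footnote on asterisks and empty cells reads "Denotes power calculation for a one-tailed test. Blank cells are underpowered to detect a significant change". No formula is named.

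The entries that matter here are:

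- Current smokers (N=482 for four schools in 2015-17, N=241 for a two-level subgroup): required n 412/603 for 55%-43%, 389/563 for 12%-5%, 411/603 for 44%-56%, 393/575 for 44%-32%, 408/596 for 32%-20% and 404/591 for 62%-50%. The last row has power 0 at N=482 and 0.83* at N=241.
- Ever smokers (N=422 in 2013-14): 408/596 for 32%-22%, and >0.80* for both 18%-25% and 18%-12%.
- All pupils (N=640 subgroup in 2013-14): 0.80 for 32%-25%, with required n 680.

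The Data analysis section adds that, because there are many outcomes, a stricter significance threshold will be used where possible.

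**The concern.** Several entries conflict on the page, before any formula is applied. The change 32%-22% needs 328/479 among all pupils but 408/596 among ever smokers, although required n depends only on the two percentages. The same 408/596 also stands against the larger change 32%-20%. That row needs 408 for 0.80 two-tailed, yet shows 0.83 at N=241 with no asterisk, so also two-tailed. The pair 404/591 serves both 62%-52% and 62%-50%.

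Table 3 is the article's statement of what the surveys can detect. Given the planned stricter threshold, readers will consult the p<.01 column. There all six current-smoker n in dispute (563 to 603) exceed 482, which suggests that these analyses cannot be run at that level. In the other direction, the two ever-smoker cells claim power that the sample does not reach.

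**Working it through.** **Inputs.** Percentages, N, alpha levels, 0.80 power and the sidedness rule all come from Table 3 and its footnote. I assume equal n in the two waves compared.

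**Identifying the method.** With d = |p1 − p2| and p̄ their mean:

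n0 = [z(1−α/2)·√(2p̄(1−p̄)) + z(0.80)·√(p1(1−p1) + p2(1−p2))]² / d²

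n = (n0/4)·[1 + √(1 + 4/(n0·d))]², rounded up.

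For 32%-25% at α = 0.05: n0 = (1.251 + 0.536)²/0.0049 = 651.6, and n = 162.9 × (1 + √1.0877)² = 679.9, so 680 as printed. At α = 0.01 it gives 999, as printed. It also returns 1239/1797 (4%-2%), 404/591 (62%-52%) and 588/859 (18%-12%). In all, 19 of 26 rows match to the unit at both alphas.

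**The seven rows that fail.** For 55%-43%: n0 = (1.386 + 0.591)²/0.0144 = 271.2, and n = 67.8 × (1 + √1.1229)² = 287.7, so 288 against a printed 412. The full set:

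| Row | Printed n | Correct n | Change that gives the printed n |
|---|---|---|---|
| Current, 55%-43% | 412/603 | 288/421 | 55%-45% |
| Current, 12%-5% | 389/563 | 276/398 | 12%-6% |
| Current, 44%-56% | 411/603 | 288/421 | 44%-54% |
| Current, 44%-32% | 393/575 | 273/398 | 44%-34% |
| Current, 32%-20% | 408/596 | 225/328 | 32%-23% |
| Current, 62%-50% | 404/591 | 284/415 | 62%-52% |
| Ever, 32%-22% | 408/596 | 328/479 | 32%-23% |

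At p<.05 the overstatement runs from 408/328 = 1.24 to 408/225 = 1.81. Dropping the correction, unpooled variance, arcsine, one-sided tests, 0.90 or 0.95 power, or reading n as a total does not reproduce both columns of any failing row.

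**Which column is stale.** Power is Φ{[(d − 1/N)√N − z·√(2p̄(1−p̄))] / √(p1(1−p1) + p2(1−p2))}. For the printed changes at N=241 it gives, in table order, 0.82, 0.83, 0.82, 0.84 (one-tailed), 0.83 (two-tailed, 32%-20%) and 0.82 (one-tailed). The table prints 0.82*, 0.85*, 0.82*, 0.84*, 0.83 and 0.83*. The power cells therefore track the printed changes, and the n columns do not.

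**Effect at p<.01.** The correct n (328 to 421) all lie below 482; the printed n (563 to 603) all lie above it.

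**Ever smokers at N=422, one-tailed (z = 1.645).**

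- 18%-25%: (0.0676 × 20.54 − 0.956)/0.579 = 0.749, power 0.773. Without correction it is 0.798. Needed n: 453, or 425 uncorrected.
- 18%-12%: (0.0576 × 20.54 − 0.831)/0.503 = 0.702, power 0.759. Without correction it is 0.788. Needed n: 470, or 437 uncorrected.

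**Two smaller items.** All pupils, 32%-25% at N=640: two-tailed power is 0.775, or 0.793 uncorrected, consistent with a required n of 680. Current smokers, 62%-50% at N=482: two-tailed power is 0.96 with or without correction, where 0 is printed.

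**The case against.** The strongest reply is that nothing of substance depends on these cells. The stale n are too large, so the error is in the cautious direction. At N=482 all six current-smoker rows exceed 0.80 at p<.05, two-tailed, for the printed changes (0.957 to 0.987). Nor did Table 3 set the sample: whole year groups, then whole schools, are surveyed, so N follows from the rolls in Table 2. The all-pupil required n, including those for incidence and prevalence, all reproduce. This stands, and it fixes the grade.

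The N=422 shortfalls are also small. Without continuity correction the first is 0.2 points and the second 1.2 points. The power formula is inferred, and it misses some cells slightly, such as 0.85* for 12%-5%. That is fair, but neither cell reaches 0.80 with or without the correction.

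The 0 cannot be a computed power, since half the sample has 0.83*. It is probably a truncated entry, or may be damage from text extraction, so little weight belongs on it.

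Two stronger readings are tempting and not supported:

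- A reader might infer that the smaller changes behind the stale n are the real targets, so that the N=241 powers are overstated. The printed powers agree with the printed changes, which rules against this.
- A reader might take the column header "4 S2 & 4 S4 from 4 schools 24 pupils each class 85% response rate" as four classes per year group per school, giving 4 × 2 × 4 × 24 × 0.85 = 653 pupils, not 1280. That is an assumed reading. Table 2 takes 100% of S2 and S4 at 188 per year group, 1504 × 0.85 ≈ 1280. About eight classes of 24 make up 188, so the class size does not contradict that N.

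**Conclusion.** The point holds as a minor correction. Seven of 26 required-n rows do not follow from their printed change and overstate the n by 24% to 81% at p<.05. For the six current-smoker rows this reverses the apparent conclusion at p<.01 for N=482. Two ever-smoker cells at N=422 should be empty under the table's own rule, being 2.7 and 4.1 points short with continuity correction. The 0.80 at N=640 is slightly high, and the 0 at N=482 should be about 0.96.

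The n result rests on the formula inferred from the 19 matching rows, but the duplicated and conflicting entries show the inconsistency without it. The power figures assume equal waves and independent pupils, as the table's own n do. The documents do not support a claim that the study is undersized on this account: no powered current-smoker cell is lost for the printed changes.

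**What to change.** Reissue Table 3 with the formula named in a footnote and used for every cell:

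- Replace the seven n pairs with the correct values tabulated above.
- Blank the 18%-25% and 18%-12% cells for ever smokers at N=422, or print 0.77* and 0.76* (0.80* and 0.79* if the stated power formula omits the continuity correction).
- Replace the 0.80 for all pupils 32%-25% at N=640 with the computed value (0.775, or 0.793 uncorrected).
- Check the 0 for current smokers 62%-50% at N=482 against the source file and print the computed value, about 0.96, or >0.80.

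The cost is recalculation and a corrected table. Recruitment, data collection and analysis are unaffected; two subgroup cells become slightly less favourable, and the current-smoker rows look better at p<.01.
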